### Randomization and blinding

Block randomization will be conducted via computer-generated codes by an independent research assistant who will pack the allocation sequence with identical sequentially numbered opaque envelopes and distribute to the researcher according to the enrolling sequence. The independent research assistant should not recruit and allocate the participants for the purpose of avoiding selection bias.

Patients will be randomly assigned to the two groups at a 1:1 ratio. At the surgery morning, just before anesthesia induction, the trained attending anesthesiologists will receive the sealed envelope and know about the grouping. They will perform anesthesia strictly following the protocol and record intraoperative information. Trained follow-up personnel will not participate in the clinical anesthesia and postoperative management, or know the records of other researchers. The researcher assistant, patients, and outcome assessors will be blinded to the allocation, intraoperative management, or perioperative information until the completion of the study analysis unless specific circumstances, such as the occurrence of a serious adverse event (SAE).

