#### Secondary outcomes include:

PFS is the duration from the surgery day to the day of first evidence of progression or death within postoperative 18 months. PFS will be evaluated by using the latest-two MRI tests and clinical evidence according to the RANO (response assessment in neuro-oncology) criteria (Supplementary Table 1) [30].Numerical rating scale (NRS) of pain intensity and sleep quality on postoperative 1 to 3 days will be evaluated. Pain intensity score in NRS is 0 to 10, 0 representing no pain and 10 representing the worst pain imaginable. Sleep quality with the NRS (0 = worst sleep, 10 = best sleep) will be used to evaluate the sleep quality at 8 to 10 a.m. every day postoperatively before discharge.Encephaloedema volume will be calculated from MRI assessed by a radiologist at 3 to 7 days postoperatively.Adverse events or complications will be recorded, including congestive heart failure, arrhythmia, myocardial ischemia or infarction, pulmonary edema, pulmonary embolism, respiratory failure, stroke, encephaloedema, hydrocephalus, pneumocranium, intracranial hematomas or infection, epilepsy, gastrointestinal hemorrhage, liver, and kidney dysfunction (Supplementary Tables 2, 3).The length of hospital stay will be calculated and analyzed.

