### Sample size calculation and statistical analysis

The sample size is estimated by using PASS 2011 software (NCCS LLC). We calculated the sample size based on the primary outcome. A two-sided Log-rank test with an overall sample size of 344 subjects (172 in the intravenous group and 172 in the inhalation group) achieves 80% power at a 0.05 significance level to detect a hazard ratio of 1.66 when the overall survival is 15 vs. 11 months in intravenous and inhalation group, respectively. The study will last for about 42 months, of which subject accrual (entry) occurs in the first 24 months with the proportion dropping out of the two groups being 0.1, respectively.

Analysis will be conducted using SPSS software (version 23.0). The Kolmogorov-Smirnov test will be used to test data normality. Normally distributed continuous variables will be described as the means with standard deviation (SD) and compared by using independent *t* tests. Non-normally distributed variables will be summarized as medians and interquartile range (IQR) and compared by using Mann-Whitney *U* tests. Categorical variables will be described as numbers (*n*) and percentage (%) and compared using chi-square or Fisher’s exact tests.

The Kaplan-Meier method will be used to describe the time-to-event data (OS and PFS), and the log-rank test will be used for comparisons. Univariate and multivariate Cox proportional hazard regressions will be used for survival analysis. Together with the anesthesia type, variables with *P*<0.1 in the univariate analysis will be regarded as candidate variables for the multivariable model. A significance level of *P*<0.05 will be used to indicate statistical significance. The imputation method will be used for dealing with missing data. The impact of missing data will be estimated by sensitivity analysis. Additionally, subgroup analysis will be undertaken to assess the association between anesthesia and the outcome according to the aCCI, KPS, EOR, WHO grade, duration of anesthesia, and whether using chemotherapy or not. No interim analysis will be done and the trial will not early terminate.

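### Pain and sleep are scored repeatedly in each patient, but the stated two-sample tests take one value per patient and no single comparison per scale is named

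*Protocol article*

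**What the plan says.** In the protocol article, the list of secondary outcomes states: "Numerical rating scale (NRS) of pain intensity and sleep quality on postoperative 1 to 3 days will be evaluated". Both scales run from 0 to 10. The same list adds that the sleep scale "will be used to evaluate the sleep quality at 8 to 10 a.m. every day postoperatively before discharge". So sleep has two schedules: three fixed days, or every day of a stay whose length differs between patients.

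The section on sample size and statistical analysis gives one rule for continuous variables. For data judged normal it reads: "Normally distributed continuous variables will be described as the means with standard deviation (SD) and compared by using independent", that is, a two-sample *t* test. For all other continuous data the Mann-Whitney test takes its place. Survival and progression are the only outcomes given a method of their own. A level of P<0.05 "will be used to indicate statistical significance". No adjustment for several days or several secondary outcomes is stated.

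The sample size of 344, or 172 per arm, "achieves 80% power at a 0.05 significance level to detect a hazard ratio of 1.66". That calculation concerns overall survival. The article gives no SD, target difference or power for pain or sleep.

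**The concern.** A *t* test or a Mann-Whitney test compares one independent value per patient. The design yields at least three correlated values per patient on each scale. The rule therefore cannot be applied until someone decides which value enters the test, and the article does not decide.

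The most natural way to follow the rule is a test on each day. That has three consequences:

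- Each scale gets three chances at P<0.05, and one favourable day could be reported as an effect on pain or on sleep.
- Normality is checked variable by variable, so one day might be compared by a *t* test and the next by a Mann-Whitney test on the same scale.
- Information shared across days is not used.

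Pooling all readings as if they came from different patients would be worse, because it ignores the within-patient correlation. For sleep even the number of readings is open: under the daily-until-discharge wording it depends on length of stay, which is itself a secondary outcome.

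**Working it through.** **Inputs from the protocol article:** 172 patients per arm ("Patients will be randomly assigned to the two groups at a 1:1 ratio"), three scoring days per scale, threshold 0.05. **Assumed, because the article gives none:** between-day correlation ρ within a patient, equal for all pairs of days; NRS SD of 2 to 3 points; for the efficiency figures, the same true effect on each day. The article has no power figure for these scales to reproduce. The 172 per arm is taken as given; whether it follows from the survival assumptions is a separate matter.

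**1. False positives from three daily tests.** With independent days the chance of at least one P<0.05 is 1 − 0.95³ = 0.143. With correlated days, the three test statistics under no effect are approximately normal with correlation ρ. The chance that at least one exceeds 1.96 in absolute value was simulated with 1,000,000 draws per ρ.

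**2. Variance of the three-day mean.** Relative to a single day, the ratio is (1 + 2ρ)/3. Its inverse is the equivalent multiple of the number of patients.

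**3. Detectable difference.** At 80% power and two-sided 0.05, in single-day SDs, it is (1.960 + 0.842) × √(2/172 × ratio). For one day (ratio 1) this is 2.802 × 0.1078 = 0.302.

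| ρ | P(at least one false positive in 3) | variance ratio | equivalent multiple of patients | detectable difference, three-day mean (SD) |
|---|---|---|---|---|
| 0 | 14.3% | 0.33 | 3.00 | 0.17 |
| 0.3 | 13.6% | 0.53 | 1.88 | 0.22 |
| 0.5 | 12.5% | 0.67 | 1.50 | 0.25 |
| 0.7 | 10.9% | 0.80 | 1.25 | 0.27 |
| 0.9 | 8.4% | 0.93 | 1.07 | 0.29 |

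For the two scales together (six tests), the figure under independence is 1 − 0.95⁶ = 26.5%; correlation lowers it.

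**4. Is a single day low-powered?** Power is Φ(δ / (SD × √(2/172)) − 1.96).

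- Difference of 1 point: above 99% at SD 2, 96% at SD 2.5, 87% at SD 3.
- Difference of 0.5 point: 64% at SD 2, 46% at SD 2.5, 34% at SD 3.
- At SD 2 and ρ = 0.5, the three-day mean raises the 0.5-point power from 64% to 81%.
- If the stated 10% dropout all occurred before scoring, leaving about 155 per arm, the single-day detectable difference would be 0.32 SD.

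A single day is therefore adequately powered for differences of about 1 point and weaker only for small ones.

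**5. When averaging loses.** If the effect is on one day only, the standardised effect of the three-day mean is (1/3)/√((1 + 2ρ)/3) of that day's effect. This is 0.46 at ρ = 0.3 and 0.37 at ρ = 0.7.

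**The case against.** The strongest reply is that the article never says each day will be tested. Its rule is generic, and a *t* or Mann-Whitney test on each patient's three-day mean fits the same wording. With complete data, that *t* test makes the same comparison as the averaged arm effect from a mixed model. This stands: day-by-day testing is the natural reading, not a stated plan. But the openness is itself the weakness, because the day or the summary can be chosen after the data are seen.

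A second reply is that an article condenses, and the summary of a repeated secondary score may be fixed in an analysis plan that is not shown. That limits the weight of the point. It does not remove it, since the article states a rule that covers these outcomes and the rule does not fit repeated scores.

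A reader might infer more than the documents support:

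- *That the daily tests are low-powered, or use a third of the data.* Each daily test uses every patient scored that day and detects about 0.30 SD. Less efficient is the accurate description.
- *That three-day analysis is always worth 1.25 to 1.9 times the patients.* This needs a similar effect on each day and ρ of 0.3 to 0.7; step 5 shows the reverse for a one-day effect.
- *That the trial's conclusions rest on these scores.* The Discussion does mention perioperative analgesia, but the stated hypothesis, the primary outcome and the sample size all concern overall survival.

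**Conclusion.** The point holds as a matter of analysis choice for two secondary outcomes. Three daily tests at 0.05 are not prescribed, but nothing in the article prevents them. They would carry a false-positive chance of about 11% to 14% per scale at ρ of 0.3 to 0.7, falling to about 8% at ρ of 0.9, instead of 5%. If effects are similar across days, one three-day comparison lowers the detectable difference from 0.30 SD to 0.22–0.27 SD at ρ of 0.3 to 0.7. The correlations and SDs are assumptions. For sleep, the count of three days holds only under the first of the two stated schedules. A change is worth making because it removes the choice of day at almost no cost.

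**What to change.** For each scale, name one test: the arm difference averaged over days 1 to 3 from a linear mixed model with arm, day and arm-by-day, and an unstructured covariance over days. Show daily values descriptively, without separate claims. Because the scores are bounded and may be skewed, add a Mann-Whitney test on each patient's three-day mean as a sensitivity analysis. State how a missing day is handled: the model uses the remaining days under a missing-at-random assumption, and this should be squared with the article's general statement on imputation.

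Reconcile the two sleep-scoring schedules so that the analysed days are the same for all patients.

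The cost is plan wording only; no new data or patients are needed. The downside is that an effect confined to one day is described and not separately claimed, and the averaged test has less power for such an effect.

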### Outcomes

The primary outcome is OS (by months) of the patients within 18 months postoperatively. OS is the duration from the day of surgery to the date of death or last follow-up. The assessment of outcomes will be performed by trained research assessors who are blinded to the group allocation. They will assess the OS through telephone interviews with patients or their relatives every 3 months postoperatively.

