## Discussion

This is a randomized controlled trial to compare the effect of intravenous or inhalation anesthesia maintenance on the OS in supratentorial HGG patients of KPS<80. There are some well-known risk factors such as age at diagnosis, KPS, histological type, distant metastasis, and extent of surgical resection for predicting the OS of patients with HG G [31].

Intravenous and inhalation anesthesias are the common anesthesia methods for HGG resection. But they are different in some aspects. Firstly, intravenous anesthesia inhibits the invasion of the tumor cells and host stress response and protects cellular immunity, while inhalation anesthesia has the opposite effect. Secondly, during craniotomy, the mass effect of the tumor and the peritumoral edema always lead to severe intracranial hypertension and brain herniation. As nearly all inhalational agents increase the cerebral blood flow and ICP, propofol has the opposite effect to decrease the ICP and facilitate tumor exposure. Thirdly, intravenous anesthesia promotes postoperative rapid recovery of the patients. Postoperative pain, nausea and vomiting, and shivering appear less frequently with propofol-maintained anesthesia [16, 33, 34]. However, the hemodynamic stability, time to extubation, and early cognitive functions were similar with two anesthetic techniques [35].

In this RCT study, we will fully evaluate the patients before operation, including physical status, neurological function, and imaging results. During the operation, standard anesthesia management, anesthesia depth monitoring, and individualized medication according to the protocol will be conducted by specially trained personnel. After surgery, the patients will be followed up regularly by designated personnel for the recovery, adverse events, complications, treatment, PFS, and OS.

Although the intervention of our study is intravenous or inhalation anesthesia, inhalational anesthetics will not be used for induction, as it is not routine in clinical practice. So propofol induction will be used in both groups. We regard the effect of a single bolus of propofol as minimal and short, which will be eliminated completely before surgical incision.

We use the survival time to calculate the sample size. As the median OS was 15 vs.11 months in TIVA and inhalation group, with a hazard ratio of 1.66, the calculated sample size is 344, which is more credible in survival analysis.

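### The OS comparison that the trial is powered on is an unadjusted log-rank test, and the only adjusted model picks its covariates by univariate P<0.1; fixing age, KPS and WHO grade in advance in a named primary model could recover some power at little cost

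*Protocol article*

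**What the plan says.** All places are in the protocol article.

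- **Primary outcome** (Outcomes): "The primary outcome is OS (by months) of the patients within 18 months postoperatively".
- **Sizing** (Sample size calculation and statistical analysis): the calculation uses a two-sided log-rank test with 172 patients per arm, 344 in all. The article states that this "achieves 80% power at a 0.05 significance level to detect a hazard ratio of 1.66". Survival is taken as 15 months under propofol and 11 months under sevoflurane, and the Discussion makes clear that these figures are medians: "As the median OS was 15 vs.11 months in TIVA and inhalation group, with a hazard ratio of 1.66".
- **Comparison of OS and PFS** (same section): Kaplan-Meier description, then "the log-rank test will be used for comparisons". No stratification factor or covariate is named.
- **Adjusted analysis** (same section): univariate and multivariable Cox regression. Anesthesia type is kept in, and other variables become candidates if their univariate P is below 0.1. The section does not say whether the log-rank test or the Cox model answers the primary question; only the sample size paragraph points to the log-rank test.
- **Allocation** (Randomization and blinding): "Block randomization will be conducted via computer-generated codes by an independent research assistant", at 1:1, with no stratification factor named.
- **Prognosis** (Discussion): "There are some well-known risk factors such as age at diagnosis, KPS, histological type", followed by distant metastasis and extent of resection.
- **Availability**: Data collection and management lists age and KPS among the items recorded before surgery. Histology and WHO grade are not in that list. WHO grade appears as a subgroup factor, and postoperative pathology is mentioned in the paragraph on analysis populations.

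**The concern.** In a survival comparison with mixed prognosis, a test that ignores strong predictors has less power than one that conditions on them, even with perfect randomisation. Here the population pools WHO grades III and IV, allocation is not stratified, and the test used for sizing conditions on nothing, although the protocol itself lists the main predictors.

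The planned Cox model does not close the gap. Its covariates are unknown until the outcome data have been looked at, it is not the analysis the trial is powered on, and its rank relative to the log-rank test is not stated. The P<0.1 screen could also admit extent of resection. The Discussion lists it as a predictor, and the Background argues that propofol may help achieve complete resection. On that reasoning it lies on the pathway from treatment to outcome and should not be adjusted for in the primary estimate.

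At stake are some points of power, and a primary result that could be read from either of two analyses.

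**Working it through.** **Inputs from the article.** N = 344 (172 per arm), two-sided alpha 0.05, power 80%, hazard ratio 1.66, medians 15 vs 11 months, 24 months of accrual in a 42-month study, dropout 0.1 per arm, outcome within 18 months.

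**Inputs that are assumptions.** The strength of age, KPS and grade, and the share of grade III (25%). Neither is in the documents, so two sets of strengths are shown.

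**Step 1: the plan's own figure.** With z = 1.960 + 0.842, z² = 7.85:

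- Schoenfeld events = 4z²/(ln HR)². At HR 1.66: 31.4/0.257, giving 123. At HR 15/11 = 1.364: 31.4/0.0962, giving 327.
- Freedman events = z²(HR+1)²/(HR−1)². This gives 128 and 332.
- N = events/p. Here p is the mean over the arms of (λ/h)·[1 − (e^(−18h) − e^(−42h))/(24h)], with h = λ + dropout hazard.

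Reading the 10% dropout as none, over 42 months, over 18 months or per year, with or without a further division by 0.9, N is 152 to 209 at HR 1.66 and 417 to 517 at medians 15 vs 11. None of these readings gives 344. The stated hazard ratio and the stated medians disagree under exponential survival, so power is shown for both.

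**Step 2: log-rank power at N = 344 without prognostic heterogeneity** (18-month follow-up, 10% dropout over 18 months). Power = Φ(√(D/4)·ln HR − 1.96).

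- Medians 15 vs 11, D ≈ 204.6 deaths: √51.15 × 0.310 − 1.96 = 0.26, so about 60%. Simulated: log-rank 61.1%, adjusted Cox 61.4%.
- HR 1.66, D ≈ 216.3: √54.1 × 0.507 − 1.96 = 1.77, so about 96%. Simulated: log-rank 96.0%, adjusted Cox 95.6%.

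When the covariates have no effect, adjustment makes essentially no difference.

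**Step 3: with prognostic effects.** Conditional hazards are exponential, covariates are independent, and the conditional hazard ratio is 1.364 (marginal medians held at 15 and 11) or 1.66. Strengths are hazard ratios per SD of age / per SD of KPS / grade IV vs III.

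- Set A (3,000 trials per setting): weak 1.2/1.2/1.5; moderate 1.35/1.3/2.0; strong 1.5/1.4/2.5.
- Set B (4,000 trials per setting): weak 1.16/1.11/1.5; moderate 1.35/1.22/2; strong 1.65/1.35/3. These correspond to log hazard ratios per SD of 0.15/0.10, 0.30/0.20 and 0.50/0.30 for age/KPS.

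| Effect | Strength | Set A: log-rank → Cox | Gain (points) | Set B: log-rank → Cox | Gain (points) |
|---|---|---|---|---|---|
| 15 vs 11 | weak | 56.7% → 59.9% | 3.2 | 59.7% → 61.2% | 1.5 |
| 15 vs 11 | moderate | 51.8% → 59.7% | 7.9 | 52.4% → 58.4% | 6.0 |
| 15 vs 11 | strong | 48.1% → 58.5% | 10.4 | 45.9% → 59.5% | 13.7 |
| HR 1.66 | weak | 94.6% → 95.8% | 1.2 | 95.1% → 95.8% | 0.6 |
| HR 1.66 | moderate | 91.5% → 94.9% | 3.4 | 92.8% → 95.7% | 2.9 |
| HR 1.66 | strong | 87.7% → 95.4% | 7.7 | 86.6% → 95.4% | 8.8 |

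The Monte Carlo standard error of a single power figure is at most √(0.25/3000) = 0.9 points for set A and √(0.25/4000) = 0.8 points for set B, so the smallest gains cannot be told from noise with confidence. In set A, a log-rank test stratified into eight prognostic cells recovered part of the gain at 15 vs 11 (56.9%, 56.0% and 55.3%).

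**The case against.** **The test is valid.** An unadjusted log-rank test in a 1:1 randomised trial keeps its type I error and matches the test used for sizing. That stands. A reader might infer that the result would be biased. It would not: an unadjusted hazard ratio nearer to 1 is the difference between a marginal and a conditional hazard ratio, and the test's error rate already allows for chance imbalance.

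**Covariates are planned.** A reader might infer that nothing in the plan conditions on prognosis. The Cox model in the next sentence of the plan says otherwise, and strong predictors would probably pass a P<0.1 screen. What remains is that its content depends on the data and its status is not stated.

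**Histology may not be complete.** A reader might infer that all three factors are collected for everyone. The documents support that for age and KPS. For WHO grade it is an inference from the subgroup list and the mention of postoperative pathology.

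**The gain cannot be sized from the documents.** True. Entry is limited to KPS below 80, which narrows what KPS can contribute. At HR 1.66, unadjusted power is at least 86.6% in every setting, already above the 80% target.

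**Covariates are usually left to an SAP.** In general, yes. But this article does fix the comparison test and does fix a covariate selection rule, and it is that stated choice which can be improved.

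**Conclusion.** The point holds as an improvement to a valid analysis, not as an error that invalidates it. The test that powers the trial ignores predictors the protocol itself names, the adjusted model is chosen from the data, and the article does not say which of the two decides.

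The gain from fixing the covariates in advance is about 1 to 14 points at medians 15 vs 11 and about 1 to 9 points at HR 1.66. It exceeds 5 points only with moderate or strong effects in the first case and only with strong effects in the second. It rests wholly on the assumed strengths, on independent covariates and on proportional hazards, so confidence in the size is low; the direction is secure if the factors predict OS at all.

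A reader might infer that adjustment rescues the trial's power. It does not. At medians 15 vs 11, adjusted power stays at about 58% to 61%, because those medians imply a hazard ratio of 1.36 and not 1.66. That mismatch is a separate matter. The change is worth making because it costs little, and it also settles which analysis is primary.

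**What to change.** In the section on sample size and statistical analysis:

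1. Name one primary OS analysis: a Cox model in all randomised patients with treatment, age (continuous), preoperative KPS and WHO grade (III, IV, other or missing pathology) as covariates fixed in advance.
2. Drop the univariate P<0.1 screen for this model, and leave out any variable that treatment could affect, such as extent of resection. Grade is read after surgery but describes a tumour present before randomisation, so it may stay in.
3. Present the unadjusted log-rank test and Kaplan-Meier curves beside it as a sensitivity analysis.
4. Use the same covariates for PFS.
5. Add WHO grade to the listed data items, so that its availability is stated and not inferred.

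The cost is wording, settled before outcome data are seen; the Trial status section says that no participant had yet been recruited. About 200 deaths are expected by 18 months for five model terms (treatment, age, KPS and two for grade), or 200/5 = 40 per term, so the model is easily supported. The downside is that the hazard ratio becomes conditional on the covariates and relies on proportional hazards, which is why the unadjusted test should stay visible.

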In the retrospective study of 294 patients with primary supratentorial HGGs undergoing elective tumor resection, anesthesia maintenance with sevoflurane did not significantly worsen the PFS of the patients compared with propofol. However, sevoflurane might decrease the OS in patients with a Karnofsky Performance Status (KPS) scale of less than 80 [12]. The KPS scale is subjectively evaluated and recorded by a neurosurgeon preoperatively based on the following hierarchical scale: 100=normal, no evidence of disease; 90=able to perform normal activity with only minor symptoms; 80=normal activity with effort, some symptoms; 70=able to care for self but unable to do normal activities; 60=requires occasional assistance, care for most needs; 50=requires considerable assistance; 40=disabled, require special assistance; 30=severely disabled; 20=very sick, requires active supportive treatment; and 10=moribund.

The OS of patients with lower KPS were more influenced by the choice of anesthetics. Several reasons might be related to the results. Firstly, sevoflurane increases cerebral blood flow and decreases the cerebral metabolic rate by decoupling of the relationship between blood flow and oxygen consumption of the brain tissue. It increases ICP and reduces the compliance of brain tissue, which aggravates the neurofunction of the lower KPS patients [13]. However, propofol reduces cerebral blood flow and cerebral oxygen consumption simultaneously, which benefits for brain tumor patients with higher ICP. Secondly, compared with sevoflurane, propofol reduces the release of inflammatory factors and vascular permeability, which may reduce the severity of encephaloedema, and contribute to the complete resection of the tumor and the early recovery of patients [14]. Lastly, propofol improves postoperative analgesia and promotes rapid recovery compared with inhalational anesthetics [15, 16]. So propofol has been recommended for better ICP control and cerebral hemodynamics of patients in neurosurgical anesthesia [17, 18]. In the retrospective study, the lower KPS patients mainly included the aged, weak, disabled, or paralyzed patients. The anesthesia methods might affect the long-term outcome through aggravating the neurofunction and systematic condition of patients, however, their effects on tumor malignancy, invasiveness, and host cellular immunity have not been identified.

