### Data collection and management

After obtaining informed consent, an independent research assistant will initiate baseline information collection one day before surgery. All personal information will be kept strictly confidential for research purposes only. Basic demographic information, including gender, age, vital signs, body mass index, past medical history, family history, smoking and drinking history, allergy history, operation history or anesthesia history, medication history, age-adjusted Charlson comorbidity index (aCCI, a widely used scoring system to predict outcomes of variety of medical conditions and malignancies, including the age of the patient as a correction variable of the final score of the CCI with the addition of one point for every decade over 40 years), ASA classification, KPS, Glasgow coma scale (GCS) will be collected. Functional classification of tumor (indicating the resectability of tumor) will be evaluated according to the results of preoperative MRI (Supplementary Table 4) [31, 32].

Intraoperative viable include vital sign parameters during anesthesia, total dose or infusion rate of anesthetic agents or other drugs during operation, such as inotropic or vasoactive drugs, mannitol, estimated blood loss, urine volume, the type, and dose of fluid and blood transfusion, duration of surgery and anesthesia. The usage of the analgesia pump (dosage, number of compressions, and effective compressions) will be recorded.

Postoperative medication will be recorded including sedative, analgesia, glucocorticoids, mannitol, and fluid infusion on 1 to 3 days postoperatively. The extent of resection (EOR) will be evaluated by a professional neuro-radiologist according to the results of the MRI within 72 h postoperatively (Supplementary Table 4).

The median follow-up time will be 18 months postoperatively before the study was terminated. The patients and their legal representatives will be told to be followed up by telephone at 3, 6, 9, 12, 15, and 18 months postoperatively. The start points of simultaneous radiotherapy and chemotherapy, patient compliance, adverse events or complications and treatment, the European organization for the research and treatment of cancer on quality of life (EORTCQLQ-C30), and the Karnofsky performance Status (KPS) Scale will be evaluated every 3 months postoperatively. Strict data management will be kept including double data entry and establishing range checks for data values.

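### The univariate P<0.1 screen for the multivariable Cox model is not limited to baseline variables, so it could admit post-randomisation variables such as extent of resection

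*Protocol article*

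**What the plan says.** The section on sample size and statistical analysis compares overall and progression-free survival by Kaplan-Meier curves, "and the log-rank test will be used for comparisons". The sample size of 344 rests on that test. The section then adds: "Univariate and multivariate Cox proportional hazard regressions will be used for survival analysis". The covariates for the multivariable model come from a screen: variables with P<0.1 "in the univariate analysis will be regarded as candidate variables for the multivariable model", together with anaesthesia type. It does not restrict the screen to variables fixed before treatment.

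Three other places matter.

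- **Timing of allocation** (Randomization and blinding): "just before anesthesia induction, the trained attending anesthesiologists will receive the sealed envelope". Whatever is measured during or after the operation is therefore post-randomisation.
- **Variables collected** (Data collection and management): these include anaesthetic and vasoactive doses, blood loss, transfusion, durations of surgery and anaesthesia, postoperative medication, the start of radiotherapy and chemotherapy, and extent of resection, read "according to the results of the MRI within 72 h postoperatively".
- **Role of resection**: the Background says that propofol lowers inflammation and vascular permeability, "which may reduce the severity of encephaloedema, and contribute to the complete resection of the tumor and the early recovery of patients". The Discussion lists among the known risk factors "age at diagnosis, KPS, histological type, distant metastasis, and extent of surgical resection for predicting the OS of patients".

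**The concern.** The trial asks what the randomised choice of anaesthetic does to 18-month survival, by whatever route. A covariate that the anaesthetic can change is part of that route, and conditioning on it removes that part from the estimate. On the article's own account, extent of resection has both features of such a variable: propofol may improve it, and it predicts survival. A screen on association with survival tends to pick strong predictors, so it favours this variable.

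Drug doses raise a related problem. The total dose of propofol or sevoflurane is largely set by the arm, so a dose covariate would compete with treatment for the same information.

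At stake is the meaning of the adjusted hazard ratio. A reader would take it as the treatment effect with prognostic imbalance removed. It could instead be a partial effect that leaves out a benefit the authors expect.

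**Working it through.** No figure in the article is at issue. The size of 344 serves only as the trial size in the illustration. The article gives no resection rates or resection effect, so these are **assumptions**, shown over a range. Hazard ratios here are propofol against sevoflurane, so values below 1 favour propofol.

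**Step 1: can such variables enter?** Set side by side, the rule has no baseline limit, allocation comes just before induction, and the collected list contains many later variables. Extent of resection, anaesthesia duration and chemotherapy are also named as subgroup factors in the same section, mixed with baseline factors such as KPS and aCCI. The rule as written allows them.

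**Step 2: hand approximation.** Let p1 and p0 be the proportions with complete resection under propofol and sevoflurane, g the hazard ratio for complete resection, and d the direct treatment hazard ratio. At the start of follow-up:

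total HR = d × [p1·g + (1 − p1)] / [p0·g + (1 − p0)]

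With p1 = 0.60, p0 = 0.40, g = 0.6 and d = 0.75: 0.75 × (0.36 + 0.40)/(0.24 + 0.60) = 0.75 × 0.76/0.84 = 0.679. A model that conditions on resection targets d = 0.75.

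**Step 3: simulation.** 344 patients, 18-month follow-up, 10% loss, 1500 replicates per row. Cox with treatment alone is set against Cox with treatment plus resection.

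| Resection, propofol vs sevoflurane | Resection HR g | Direct HR d | Hand total HR | HR without resection | HR with resection | Resection passes P<0.1 | Power without / with |
|---|---|---|---|---|---|---|---|
| 50% vs 50% | 0.6 | 0.75 | 0.750 | 0.753 | 0.746 | 97% | 0.514 / 0.521 |
| 55% vs 45% | 0.6 | 0.75 | 0.713 | 0.716 | 0.747 | 99% | 0.633 / 0.529 |
| 60% vs 40% | 0.6 | 0.75 | 0.679 | 0.685 | 0.751 | 99% | 0.755 / 0.516 |
| 60% vs 40% | 0.6 | 0.80 | 0.724 | 0.730 | 0.802 | 99% | 0.615 / 0.330 |
| 65% vs 35% | 0.6 | 0.80 | 0.688 | 0.688 | 0.797 | 99.5% | 0.756 / 0.332 |
| 60% vs 40% | 0.6 | 1.00 | 0.905 | 0.899 | 0.998 | 98% | 0.123 / 0.050 |
| 55% vs 45% | 0.8 | 0.75 | 0.734 | 0.733 | 0.747 | 59% | 0.622 / 0.555 |

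Hand and simulated totals agree closely. The Monte Carlo error of a power near 0.5 is about √(0.5 × 0.5/1500) = 0.013.

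**Step 4: share of the effect lost, on the log scale.** For 60% vs 40% with d = 0.75: 1 − ln(0.751)/ln(0.685) = 1 − 0.286/0.378 = 0.24, about a quarter. For 55% vs 45% with g = 0.6: 1 − 0.292/0.334 = 0.13. With equal resection nothing is lost.

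**The case against.** The other side has four fair points.

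- **The text says candidates only.** Extent of resection, duration and chemotherapy are named as subgroup factors, never as Cox covariates, and the list of screened variables may sit in an analysis plan that is not shown. A reader might infer that these variables will enter and will dilute the effect. The article does not support that. Entry depends on what is screened and on the data, and dilution needs resection to differ by arm, which the Background puts only as a possibility. What remains is that the rule as written permits it.
- **The log-rank test is untouched.** It is the powered test and the stated comparison, and no covariate screen can alter it. A reader might infer from the log-rank and Cox analyses standing together that success could be claimed on either, with an inflated type I error. The article states no such success rule. The harm is confined to the multivariable Cox estimate.
- **Screening on outcome does little harm when the variables are baseline.** A reader might infer that the selection itself invalidates the inference. In 2000 null trials with five prognostic and five noise baseline covariates (assumed), the screened adjusted test rejected in 5.8% against 5.5% unadjusted. With ten noise covariates it was 4.5% against 4.6%. The Monte Carlo error is about 0.5 points. The issue is therefore the missing limit to pre-treatment variables.
- **An adjusted primary analysis is not required.** Making a Cox model primary would replace the test on which the trial was sized. That is a debatable trade-off, and this point does not call for it.

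**Conclusion.** The concern holds in a limited form. The covariate rule is open to post-randomisation variables, and by the article's own reasoning extent of resection is both a plausible mediator and a likely survivor of the screen. If it enters and differs by arm, the adjusted hazard ratio is no longer the total effect of the anaesthetic.

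The loss ranges from none (equal resection) through about a quarter of the log hazard ratio (0.685 to 0.751 at 60% vs 40%) to practically all of it if resection is the only route (0.899 to 0.998). These sizes rest entirely on assumed resection rates and effects. The chance that resection passes the screen also depends on them: about 99% at a resection hazard ratio of 0.6 with 60% vs 40%, and 59% at 0.8 with 55% vs 45%. The primary log-rank comparison stands. The rule should be changed, but it does not undermine the trial's main test.

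**What to change.** 1. Delete the P<0.1 rule.
2. State that the log-rank test, on which the sample size is based, is the primary comparison of overall survival.
3. Fit one supportive adjusted Cox model with treatment plus a short pre-specified list of pre-treatment covariates, for example age, KPS, preoperative functional tumour classification and WHO grade. WHO grade is read after surgery but is a property of the tumour fixed before treatment.
4. Exclude extent of resection, chemotherapy, anaesthesia duration and drug doses from that model, and label any analysis that uses them, including the planned subgroups, exploratory.

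The cost is wording in the analysis section. All the variables are already collected, and neither sample size nor conduct changes. The change should be made before outcome data are seen; the Trial status section reports that nobody had yet been recruited.
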